# Cardiovascular risk and mortality in end-stage renal disease patients undergoing dialysis: sleep study, pulmonary function, respiratory mechanics, upper airway collapsibility, autonomic nervous activity, depression, anxiety, stress and quality of life: a prospective, double blind, randomized controlled clinical trial

**DOI:** 10.1186/1471-2369-14-215

**Published:** 2013-10-08

**Keywords:** Chronic kidney disease, Dialysis, Sleep, Quality of life

## Abstract

**Background:**

Chronic kidney disease (CKD) is one of the most serious public health problems. The increasing prevalence of CKD in developed and developing countries has led to a global epidemic. The hypothesis proposed is that patients undergoing dialysis would experience a marked negative influence on physiological variables of sleep and autonomic nervous system activity, compromising quality of life.

**Methods/Design:**

A prospective, consecutive, double blind, randomized controlled clinical trial is proposed to address the effect of dialysis on sleep, pulmonary function, respiratory mechanics, upper airway collapsibility, autonomic nervous activity, depression, anxiety, stress and quality of life in patients with CKD. The measurement protocol will include body weight (kg); height (cm); body mass index calculated as weight/height^2^; circumferences (cm) of the neck, waist, and hip; heart and respiratory rates; blood pressures; Mallampati index; tonsil index; heart rate variability; maximum ventilatory pressures; negative expiratory pressure test, and polysomnography (sleep study), as well as the administration of specific questionnaires addressing sleep apnea, excessive daytime sleepiness, depression, anxiety, stress, and quality of life.

**Discussion:**

CKD is a major public health problem worldwide, and its incidence has increased in part by the increased life expectancy and increasing number of cases of diabetes mellitus and hypertension. Sleep disorders are common in patients with renal insufficiency. Our hypothesis is that the weather weight gain due to volume overload observed during interdialytic period will influence the degree of collapsibility of the upper airway due to narrowing and predispose to upper airway occlusion during sleep, and to investigate the negative influences of haemodialysis in the physiological variables of sleep, and autonomic nervous system, and respiratory mechanics and thereby compromise the quality of life of patients.

**Trial registration:**

The protocol for this study is registered with the Brazilian Registry of Clinical Trials (ReBEC RBR-7yhr4w and World Health Organization under Universal Trial Number UTN: U1111-1127-9390 [http://www.ensaiosclinicos.gov.br/rg/RBR-7yhr4w/]).

## Background

Chronic kidney disease (CKD) is one of the most serious public health problems. The increasing prevalence of this disease in developed and developing countries has led to a global epidemic. Current epidemiological surveys suggest that approximately 1 million individuals with terminal CKD have undergone kidney replacement therapy worldwide. A large part of this epidemic may be explained by the increase in the number of diabetes mellitus cases and the increase in life expectancy. Diabetic nephropathy is expected to affect approximately 5.4% of the world population by 2015 [1].

CKD is defined as the presence of kidney damage or reduced kidney function for ≥3 months, regardless of the diagnosis. The advanced stage of this condition is known as terminal CKD or end-stage kidney disease, with progressive and irreversible loss of kidney function [2].

CKD is classified on the basis of the glomerular filtration rate (GFR), as recommended by the US National Kidney Foundation Kidney Disease Outcomes Quality Initiative, which provides the basis for the management of this disease. CKD is classified into 5 stages: stage 1, kidney damage with normal or increased GFR ≥ 90 mL/(min·1.73 m^2^); stage 2, kidney damage with mildly decreased GFR of 60 to 89 mL/(min·1.73 m^2^); stage 3, moderately decreased GFR of 30 to 59 mL/(min·1.73 m^2^); stage 4, severely decreased GFR of 15 to 29 mL/(min·1.73 m^2^); and stage 5, kidney failure with a GFR < 15 mL/(min·1.73 m^2^). Evidence of kidney damage for ≥3 months is required for the diagnosis of stage 1 and 2 CKD, as manifested by pathological kidney abnormalities or abnormal urine composition (such as haematuria or proteinuria) or abnormalities on imaging tests [3].

The prevalence rate of sleep disorders in patients with CKD ranges from 40% to 80%, which is higher than those in the general population [4]. The most frequent comorbidities include diabetes mellitus type 2 [1], periodic leg movements during sleep [4], obstructive sleep apnea (OSA) and nocturnal hypoxemia [5], dyslipidaemia, coronary disease, heart failure [6,7], systemic arterial hypertension [8,9], respiratory disorders [10,11], stress[12 ], depression [12-14], anxiety [15].

OSA is a respiratory disease characterised by the collapse of the upper airways during sleep in predisposed subjects. After chronic obstructive pulmonary disease and asthma, OSA is the most important and widespread respiratory disease, affecting 3% to 7% of the male population and 2% to 5% of the female population between 40 and 65 years of age in the Western world [16]. In Brazil, the prevalence of OSA is even higher at 24.8% in men and 9.6% in women, according to a recent epidemiological study conducted in the city of São Paulo [17].

The causal association between OSA and CKD or whether the 2 diseases result from a common pathophysiologic process has not yet been clarified. Uremic milieu has been implicated as a cause of OSA in patients with CKD. Altered ventilatory drive and chemoreceptors can lead to decreased respiration via a blunted response to ventilatory stimuli, such as hypoxia or acidaemia. Upper airway obstruction can occur from localised oedema or the collapse of the dilator muscles, leading to an increased risk of OSA. Suppression of the respiratory musculature due to metabolic acidaemia/acidosis, osmotic disequilibrium, and a reduction in middle molecule clearance could potentially cause or contribute to OSA [18].

### Aims and hypotheses

The present study involving patients with CKD was designed with 4 main objectives: (1) to assess the effects of dialysis on sleep parameters and determine the prevalence and severity of sleep disorders; (2) to determine the behaviour of sympathetic and parasympathetic autonomic nervous system activity through an analysis of heart rate variability; (3) to detect upper airway collapsibility as a risk indicator for OSA; and (4) to evaluate levels of depression, anxiety, stress and quality of life. Our hypothesis is that the weather weight gain due to volume overload observed during interdialytic period will influence the degree of collapsibility of the upper airway due to narrowing and predispose to upper airway occlusion during sleep, and to investigate the effects of nocturnal hemodialysis compared to daytime hemodialysis and the influences in the physiological variables of sleep, autonomic nervous system (ANS), and respiratory mechanics and thereby compromise the quality of life in chronic kidney diseases and end-stage renal disease patients undergoing dialysis.

## Methods/Design

### Study design

A prospective, consecutive, double-blind, randomized controlled clinical trial is proposed to investigate the effect of dialysis on sleep, pulmonary function, respiratory mechanics, upper airway collapsibility, ANS, depression, anxiety, stress and quality of life in end-stage renal disease patients, as summarised in Figure 1.

**Figure 1 F1:**
[figure not shown]
Flowchart of the study protocol.

### Subjects

The participants will be recruited from the Centro de Nefrologia Zona Norte (São Paulo, Brazil) and sent to the Sleep Laboratory of the Universidade Nove de Julho (São Paulo, Brazil). Patients will be recruited consecutively and screened for eligibility using a standardised protocol. The following will be used as the inclusion criteria: male or female patients aged 18 to 80 years; chronic kidney failure; candidate for kidney transplant with indication for dialysis; cognitive level sufficient for understanding the procedures and following the instructions; and agreement to participate by signing a statement of informed consent. Meanwhile, the following will used as the exclusion criteria: craniofacial abnormalities; undergoing active treatment of sleep apnea; active malignancy; active alcohol and/or drug abuse; and dementia or treatment-refractory psychiatric diseases leading to an inability to provide informed consent.

### Randomization

After the initial assessment and compliance with eligibility criteria, participants will be randomized into two intervention group [patients achieving diurnal hemodialysis and nocturnal hemodialysis] and the control group [CKD not submitted to dialysis]. Randomization numbers will be generated using a randomization table at a central office. A series of numbered, sealed, opaque envelopes will be used to ensure confidentiality. Each envelope will contain a card stipulating to which group the subject will be allocated.All patients underwent randomization protocol that will meet the eligibility criteria and be clinically stable.

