### Evaluation protocol

#### Clinical evaluation

Patients with chronic kidney diseases and end-stage renal disease undergoing dialysis, based on recommended procedures, will be submitted to general physical measurements performed by a well-trained physician and physical therapist before and after the dialysis session using precise instruments. The measurement protocol will include body weight (kg); height (cm); body mass index (BMI) calculated using the formula weight/height^2^[16]; circumferences (cm) of the neck, waist, and hip [20]; heart and respiratory rates; blood pressures; Mallampati index [21]; tonsil index [22]; heart rate variability [23]; maximum ventilatory pressure; negative expiratory pressure (NEP) test; and polysomnography (PSG; sleep study), as well as the administration of specific questionnaires addressing sleep apnea, excessive daytime sleepiness [24,25], symptoms of stress [12], and depression [12-14], anxiety [15], and quality of life [26,27].

The following data will be obtained from medical charts: biochemical values, associated pathological conditions, laboratory values (iron, intact-parathyroid hormone, haemoglobin, calcium, phosphorus, and creatinine), duration of dialysis therapy, comorbidities, and aetiology of kidney disease.

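### The only inclusion list requires an indication for dialysis, yet patients who meet it are randomised to a control group that is not dialysed

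*Protocol article*

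**What the plan says.** The Subjects section of the protocol article sets out a single list of inclusion criteria, joined so that all must be met. One of them is "candidate for kidney transplant with indication for dialysis". No separate list is given for controls.

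The Randomization section opens: "After the initial assessment and compliance with eligibility criteria, participants will be randomized into two intervention group", namely diurnal and nocturnal haemodialysis, "and the control group [CKD not submitted to dialysis". The group is assigned by a card in a numbered, sealed, opaque envelope, with no exception for controls. The section closes by repeating the eligibility condition: "All patients underwent randomization protocol that will meet the eligibility criteria and be clinically stable".

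The Study design section presents a randomised controlled trial "to investigate the effect of dialysis on sleep" and other outcomes, in patients with end-stage renal disease. Aims and hypotheses names a narrower contrast: "to investigate the effects of nocturnal hemodialysis compared to daytime hemodialysis".

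**The concern.** Eligibility and allocation together decide who enters the trial, what care they receive and which comparison may be called causal. Here a control patient must have an indication for dialysis in order to be randomised, and must be undialysed in order to be a control. Site staff cannot apply both rules and still give that patient the indicated treatment.

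What is at stake is the status of the control group. If its members did not come from the same eligible pool by chance, a difference between them and the dialysed patients reflects the reasons for starting dialysis as well as dialysis itself. The Study design section would nevertheless lead a reader to treat that difference as a randomised estimate.

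**Working it through.** The point rests on the text; no sample-size or power figure is needed. The rules, set side by side:

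1. **Subjects:** eligible implies an indication for dialysis.
2. **Randomization, first and last sentences:** randomised implies eligible.
3. **Randomization, group definitions and envelopes:** control implies randomised, and control implies not dialysed.

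Chaining them: control → randomised → eligible → indication for dialysis. Every control therefore has an indication for dialysis and is not dialysed. Avoiding that conclusion means giving up one of the written rules, so there are two cases.

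**Case A: controls are CKD patients without an indication.** Rule 1 fails for them, so by rule 2 they cannot have been randomised. They could not properly have drawn a dialysis card, and a patient with an indication could not properly have drawn a control card. Under this reading the indication is present in 100% of dialysed patients and 0% of controls. That is true by definition and is not a measured imbalance. With no overlap on the indication, adjusting for measured covariates cannot recover a randomised comparison of dialysis with no dialysis.

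**Case B: controls come from the eligible pool.** Randomisation is then intact, but patients with an indication are allocated to no dialysis. The article does not say for how long or how they are managed.

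**Does other text decide between the cases?**
- Aims and hypotheses refers to "chronic kidney diseases and end-stage renal disease patients undergoing dialysis". The closing words can qualify both diagnoses, so this is only weak evidence that undialysed CKD patients were meant. Study design names end-stage renal disease alone.
- The bracketed definition of the control group is the best support for case A, but it says nothing about indication.
- Clinical evaluation says that patients "will be submitted to general physical measurements performed by a well-trained physician and physical therapist before and after the dialysis session", and polysomnography and the negative expiratory pressure test are also timed around haemodialysis. An undialysed patient has no session. This suggests that the control group was not worked through, but it does not settle which case applies.

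**Extent.** One of three groups is involved. The sample-size section gives 57 patients without saying whether that is the total or the number per group. Assuming equal allocation, the control group is 57/3 = 19 patients if 57 is the total, and 57 if it is per group.

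**What is untouched.** Diurnal versus nocturnal haemodialysis compares two dialysed groups, both of which can satisfy rules 1 to 3. Before/after-session measurements are made within dialysed patients. Neither depends on how controls were recruited.

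**The case against.** Four points can fairly be made on the other side.

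- **A journal article condenses the full protocol, and the flowchart (Figure 1) is not shown.** The flowchart may show separate recruitment of controls. But the problem is not something left out: the article states both rules, and they conflict. A figure could show the intention but would not change the two sentences.
- **The indication might mean a future need for dialysis.** The article does not say so. If it did, patients with no present need would be sent to dialysis by envelope, which is no better.
- **The statistical section names no test of dialysis against control.** It lists comparisons between shifts, comparisons of patients with and without obstructive sleep apnoea, correlations, logistic regression and ROC curves. This stands, and it limits the harm to any comparison that does use the control group and to describing that group as randomised. It does not remove the harm, because the Study design section makes the effect of dialysis the subject of a randomised trial.
- **The choice between cases A and B is uncertain.** This also stands. Confidence is high in the contradiction, but not in which case was intended.

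A reader might go further and infer that the trial deprives control patients of dialysis they need. The documents do not support that. It follows only in case B, which is the less plausible reading. Even there no duration is given, and a short period of assessment before dialysis starts is not excluded.

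**Conclusion.** The contradiction is real and explicit: the inclusion list and the randomisation rule cannot both hold for a control patient who receives indicated care, and nothing else in the article reconciles them. It concerns one of three groups: 19 to 57 patients, on the assumption of equal allocation and depending on how 57 is read. As written, the control group either is not randomised, so that dialysis versus no dialysis is confounded by indication, or consists of patients with an indication who go undialysed for an unstated period.

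A reader might also infer that the whole trial loses its randomised basis. It does not: the contrast between diurnal and nocturnal haemodialysis stands. Whether 57 patients are enough, and for which comparison, is a separate matter on which this conclusion does not depend.

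The text needs correcting, because it governs who may be enrolled and what the control group can be used to show.

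**What to change.** 1. **Randomization:** restrict the envelopes to diurnal versus nocturnal haemodialysis, among patients who have an indication for dialysis and can receive either schedule.
2. **Subjects:** keep the present list for the randomised patients and add a separate eligibility line for the undialysed group: CKD without a current indication for dialysis.
3. **Study design:** describe the undialysed group as a concurrent non-randomised comparator.
4. **Analysis and reporting:** present dialysis versus no dialysis as an association with residual confounding by indication. Reserve randomised language for diurnal versus nocturnal.

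The cost is an amendment to the eligibility, randomisation and design text, and a weaker claim about the effect of dialysis. No new measurement is required to remove the contradiction. The Randomization and Haemodialysis sections are partly in the past tense; if enrolment has already begun, the route by which each enrolled patient entered their group should also be documented.

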### Blinding

Baseline data will be collected prior to randomisation so that trial investigators, assessors, research co-ordinators and trial participants will be blinded to allocation while the data is being collected. Blinding will be maintained in all steps of the research.

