#### Polysomnography

All the patients will undergo a standard overnight PSG (Embla, A10 version 3.1.2 Flaga, Hs. Medical Devices, Reykjavik, Iceland) at the Sleep Laboratory of Nove de Julho University*.* Polysomnography exams will be held the night before the haemodialysis and approximately 12 hours after this dialysis. All recording sensors will be attached to the patient in a non-invasive manner using tape or elastic bands. The following physiological variables will be monitored simultaneously and continuously: 4 channels for the electroencephalogram (C3-A2, C4-A1, O1-A2, and O2-A1), 2 channels for the electrooculogram (EOG-Left-A2 and EOG-Right-A1), 4 channels for the surface electromyogram (muscles of the submentonian region, anterior tibialis muscle, masseter region, and seventh intercostal space), electrocardiogram (derivation V1 modified), airflow detection via 2 channels through a thermocouple and nasal pressure cannula, respiratory effort of the thorax and abdomen via x-trace belts, snoring and body position sensors, and arterial oxygen saturation and pulse rate via an oximeter.

All the subjects will be monitored by a technician experienced in PSG. Sleep stages will be visually scored in 30-s epochs, and each PSG recording will be analysed manually under blinded conditions by the same examiner with experience in scoring PSG recordings in accordance with international standards established by the Academy of Sleep Medicine Manual for Scoring Sleep and Associated Events. The patients will be instructed to remain as relaxed as possible and sleep naturally, as if at home. All signals will be recorded continuously [34,35].

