#### NEP test

The NEP test will be conducted before and after hemodialysis sessions, performed through the administration of a negative pressure at the mouth during expiration. This is a practical test performed while awake and requires little cooperation from the subject. In the absence of expiratory flow limitation, the increase in the 8 pressure gradients between the alveoli and the open upper airway caused by NEP results in an increase in expiratory flow.

NEP will be generated by the Super Air Amplifier (Exair model 120021, Cincinnati, OH, USA) coupled to a tank of compressed air via an electrically operated solenoid valve (model 95004, Norgren Ltd; Vimercate, MI, Italy) automatically activated in early expiration and kept open for 2 s by software control (Figure 2). A pneumotachograph (Hans Rudolph model 3830; Kansas, MO, USA) will be connected to the air amplifier and the mouthpiece to measure airflow ($\dot{V}$) with pressure transducers (PCLA02X5; Sensortechnics GmbH, Puchheim, Germany). Mouth pressure will be measured by pressure transducers (PCLA0050; Sensortechnics GmbH, Puchheim, Germany). NEP of 10-cm H_2_O will be set by occluding the pneumotachograph with a stopper and adjusting the flow of compressed air-to-air amplifier (Figure 2).

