### Study interventions

#### Haemodialysis

Regular daytime or nocturnal haemodialysis was standardised during the trial. It was performed 3 times per week, with a 4-h session duration, 250-mL/min blood flow, and 500-mL/min dialysate flow, using bicarbonate-buffered dialysate with 1.25 mmol/L ionised calcium concentration, dialysate temperature of 36.5°C, and Polyflux 17-L dialyser [42].

The ultrafiltration amount for each haemodialysis session was decided by individual dry weight, which was fixed during the trial. In addition, during the trial, the patients were not permitted to change their medication or start new drugs, especially antiplatelet agents, angiotensin-converting enzyme inhibitors, angiotensin II receptor antagonists, calcium-channel blockers, and β-blockers.

The patients who required a change in medication for medical reasons were subsequently excluded from the study. Use of *N*-acetylcysteine was also prohibited in view of its potential influence on ischemia-reperfusion injury.

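### The trial is called double-blind with blinding in all steps, but a comparison of daytime, nocturnal and no haemodialysis without a sham is open-label after allocation; the only later blinding described is of polysomnography scoring

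*Protocol article*

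**What the plan says.** The design label, in the Study design section and likewise in the title and abstract, is: "A prospective, consecutive, double-blind, randomized controlled clinical trial is proposed".

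The Blinding section gives one mechanism, the collection of baseline data before randomisation. From this it concludes that "trial investigators, assessors, research co-ordinators and trial participants will be blinded to allocation while the data is being collected", and it adds: "Blinding will be maintained in all steps of the research".

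The Randomization section defines the groups: "participants will be randomized into two intervention group [patients achieving diurnal hemodialysis and nocturnal hemodialysis] and the control group [CKD not submitted to dialysis". It provides numbered, sealed, opaque envelopes. The Haemodialysis section describes what the dialysed patients receive: "Regular daytime or nocturnal haemodialysis was standardised during the trial. It was performed 3 times per week, with a 4-h session duration". Neither section describes a sham or any other masking.

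The Clinical evaluation section places its physical measurements before and after the dialysis session. The NEP test section says the same of that test: "The NEP test will be conducted before and after hemodialysis sessions".

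The Polysomnography section contains the only concrete blinding measure after baseline: "each PSG recording will be analysed manually under blinded conditions by the same examiner".

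**The concern.** A patient knows whether he or she is dialysed three times a week, and whether this happens by day or by night. So do the staff who give the dialysis and anyone who measures around a session. The claim of blinding in all steps therefore conflicts with the document's own groups and procedures.

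The outcomes most exposed are those that the patient answers or produces by effort. Depression, anxiety, stress and quality of life make up the fourth main objective under Aims and hypotheses. They are measured with the Beck inventory, the Hamilton anxiety scale, the stress inventory and the SF-36. The Epworth scale and the Berlin questionnaire also depend on the patient's answers, and spirometry and maximal ventilatory pressures depend on cooperation and effort. The abstract expects dialysis to have a negative influence, so patients and staff may share a directional expectation. A reader told that the trial is double-blind would not allow for this.

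**Working it through.** The plan gives no figure for blinding, so there is none to reproduce. The main check sets the statements side by side.

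**1. Who could be blind, and when**

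| Role | What the article describes | Can be blind after allocation? |
|---|---|---|
| Participants | Daytime, nocturnal or no dialysis; 4-h sessions, 3 times a week; no sham | No |
| Staff giving dialysis | Same | No |
| Those taking clinical measurements and the NEP test | Measured before and after the session | No |
| Those performing spirometry | Done during the day; no link to a session stated | Not determined by the text; the patient is still aware |
| Polysomnography scorer | Manual scoring under blinded conditions | Yes |
| Everyone, at baseline | Baseline collected before randomisation | Allocation unknown at that point |

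Sealed envelopes and baseline measurement before randomisation conceal the coming allocation. Neither keeps anyone unaware of it afterwards. The Blinding section thus extends a baseline safeguard to the whole study.

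**2. Illustration of what an expectation shift could do**

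Inputs:
- 57 patients in total (Sample size calculation and statistical analysis section).
- Three groups (Randomization section).
- Assumed: equal allocation, so 57/3 = 19 per group. The article gives no ratio.
- Assumed: no true effect, a normally distributed scale, and an expectation shift d of 0.2, 0.3 or 0.5 SD.
- Two-sided 5% level.

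(a) *One-way ANOVA*, which the article plans for comparisons between shifts. There are 2 and 54 degrees of freedom, the critical F is 3.168, and the noncentrality is λ = 19 × Σ(mᵢ − m̄)².
- Both dialysis groups shifted equally against control (0, d, d): λ = 19 × (2/3)d² = 0.507, 1.140, 3.167. Rejection is 8.8%, 14.0%, 32.1%. One group shifted alone gives the same values.
- Graded shift (0, d/2, d): λ = 19 × d²/2 = 0.380, 0.855, 2.375. Rejection is 7.8%, 11.6%, 24.9%.

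(b) *Two-sample t-test* between two groups, for comparison. There are 36 degrees of freedom, the critical value is 2.028, and the noncentrality is d × √(19/2) = 0.616, 0.925, 1.541. Rejection is 9.2%, 14.7%, 32.3%.

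Over these patterns the nominal 5% becomes about 8–9%, 12–15% and 25–32%.

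**The case against.** Parts of the plan are sound. Baseline data are collected before allocation is known. The apnoea/hypopnoea index, the only outcome used for the sample size, comes from recordings scored blind. The heart-rate-variability system is described as fully automatic, and NEP signals are analysed by software, so there is less reader judgement to protect. Patients are recruited at a nephrology centre and studied at a separate sleep laboratory, so not every assessor need know the group. All of this stands. None of it makes the claim true for participants, and a fuller protocol could not do so either.

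Three stronger readings are tempting and are not supported:

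- *No staff can be blind.* The polysomnography scorer can be. For spirometry the text does not settle whether the assessor knows the group.
- *The questionnaires should be demoted and the apnoea/hypopnoea index made the main endpoint.* The article lists depression, anxiety, stress and quality of life among four main objectives and names no single primary endpoint. Lack of blinding calls for a stated limitation, not a new ranking.
- *The percentages measure the error, and the fix would bring them back to 5%.* They rest on assumed shifts and an assumed 19 per group. The upper values also depend on the pattern of the shift. A new label leaves the bias where it is.

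**Conclusion.** The statement is wrong as written. After allocation the trial is open-label for patients, for treating staff and for those measuring around sessions. What the article supports is concealment of allocation at baseline and blinded scoring of polysomnography. This conclusion follows from the text alone and needs no calculation.

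The illustrative rates only show that a modest expectation effect would not be negligible in groups of this size. Their real size is unknown, because the article gives no basis for the shift. The practical consequence is for interpretation: group differences on questionnaires and effort-dependent tests would be presented with a protection they do not have. The planned analyses and the sample size are not affected.

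**What to change.** - In the title, abstract and Study design section, replace double-blind with: open-label, with baseline assessment before allocation and blinded scoring of polysomnography.
- In the Blinding section, delete the claim about all steps and name the roles that are blinded and at which stage.
- State that the Epworth, Berlin, stress, Hamilton anxiety, Beck and SF-36 outcomes and the effort-dependent tests (spirometry, maximal ventilatory pressures) are unblinded. Add that group differences on them will be interpreted with possible expectation bias in mind.
- Where a person handles stored NEP or heart-rate-variability files or the analysis dataset, use group codes in place of group names.
- Leave the ranking of objectives and endpoints as it is.

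The cost is a few changes of wording and, where they apply, coded labels. No measurement, analysis or sample size changes.
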